## Abstract

**Introduction:**

Psoriasis (PSO) is a disease that in the majority of patients is accompanied by itch, which imposes a great burden and positively relates to anxiety. *Social* anxiety, a facet of anxiety associated with social withdrawal, may be a predictor of itch intensity in this patient group. Moreover, anxiety is linked to the secretion of neuroendocrine and inflammatory parameters such as substance P (SP), interleukin (IL)-6 and IL-17, which are also related to itch. In this research project, we investigate first, whether there is a direct relationship between social anxiety and itch intensity in patients with PSO and second whether the secretion of SP, IL-6 and IL-17 in the skin mediates this relationship. Additionally, PSO-patients are compared to healthy skin controls regarding their level of social anxiety, itch intensity and the secretion of SP, IL-6 and IL-17.

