### Objectives

The first aim of the research project is to investigate whether social anxiety is a predictor of itch in PSO-patients (study 1). The second aim of this research project is to answer the question whether IL-6, IL-17 and SP mediate the relationship between social anxiety and itch intensity in PSO-patients. In addition, we investigate, whether healthy skin controls and PSO-patients differ regarding social anxiety and/ or the release of SP, IL-6 and IL-17 (study 2; also see spirit schedule, Fig 1)

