### Psychometric measures

#### 1) Social anxiety

Social anxiety is measured in both studies by means of the *social anxiety disorder scales* (SOZAS) [67]. These include the *social interaction anxiety scale* (SIAS) and the *social phobia scale* (SPS). Both are validated German questionnaires, which contain 20 items each that need to be answered on a 5-point scale. The SIAS measures interactional anxiety, the SPS measures anxiety in evaluation situations. The items in both questionnaires do not refer to a specific time period. In this research project, subjects will be categorized as being either high (HSA) or low (LSA) socially anxious according to a median split of the SIAS scores in order to determine whether these groups differ in itch intensity and the secretion of assessed neuroendocrine and inflammatory parameters.

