### Statistical analyses

Statistical analyses will be performed using SPSS and the macro PROCESS for SPSS [86–88]. In order to answer research question of study 1, Spearman’s rank-order correlation analyses will be conducted first in order to see which of the control variables are significantly related to itch intensity in PSO patients. These will then be included in step 1 of the subsequent linear hierarchical regression model. Social anxiety measured by the SIAS and SPS will be considered as predictor variable in step 2 of the analyses. Maximum and average itch intensities represent the criterion variables

To answer the research question of study 2, mediation analyses will be conducted using the SPSS macro PROCESS [86–88]. In these analyses, control variables significantly associated with itch intensity as well as social anxiety will be included as possible predictor variables, neuroendocrine and inflammatory parameters as mediators, and average as well as maximum itch intensity as criterion variables. If we find significant correlations between maximum induced itch, and the neuro-inflammatory parameters, we will exploratively conduct a regression analysis with the maximum induced itch as end-point.

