Separate analyses will be conducted for patients and controls. To determine the required sample size, we performed an analysis using G*Power [89] to extrapolate the sample size for study 2. Based on correlational studies regarding itch and anxiety [33] as well as on neuroinflammatory parameters and itch [52] in PSO-patients we expect small to medium sized effects (f^2^ = .10). The estimation with an α of 0.05 and a β of 20 revealed that 64 healthy skin controls and 64 PSO-patients are to be included in study 2. Small to moderate effects can be assumed because, on the one hand, only extreme groups are examined and, on the other hand, small to moderate correlations between anxiety and itch intensity (*r* = .179; *p* = .003) have been found in PSO-patients [33] and between neuroinflammatory parameters and itch intensity (*r* = .60; *p* < .01) [52]. In case, that patient recruitment for the studies is slower than anticipated, we would aim to gather additional personnel and material resources to improve the recruitment rate over time. Since study 2 has more strict inclusion and exclusion criteria on e.g. medication and comorbidities than study 1 (see inclusion and exclusion criteria), we expected a reduction in participants who match these premises. In addition, motivational factors are to be considered, as in contrast to study 1, study 2 will be conducted in a laboratory setting. We therefore estimated that n = 500 participants need to be included in study 1 to achieve the calculated sample size of n = 128 participants for study 2. As there is no cut-off value in the user manual of the SIAS [90] to categorize somebody as low socially anxious, we planned to use percent range ≤ 25 in order to categorize 32 participants per group as being low socially anxious. Due to the pandemic situation, participant recruitment during the course of 2020 and 2021 was and still is very difficult. Therefore, we had to change this inclusion criterion for study 2 and now invite all participants of study 1 irrespective of their social anxiety scores to take part in study 2. High and low socially anxious participants will now be identified by median split. Statistical analyses will be conducted when the targeted sample size (study 1: *N* = 500, study 2: *N* = 128) has been achieved or further inclusion of participants is no longer possible due to the end of funding. No intermediate data analysis is planned. Data collection started after ethic approval in December 2020 for study 1 (number of currently assessed patients n = 234; number of currently assessed healthy controls n = 174), and in September 2021 for study 2 (number of currently assessed patients n = 27; number of currently assessed healthy skin controls n = 15). Data collection will be continued until the planed sample sizes are reached or as long as funding is available.

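### The patient-control comparison of social anxiety is assigned to study 2 (64 vs 64) although study 1 measures it in 250 vs 250, and the models described do not estimate it

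*Protocol article*

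**What the plan says.** The introduction in the Abstract states that "PSO-patients are compared to healthy skin controls regarding their level of social anxiety, itch intensity and the secretion of SP, IL-6 and IL-17". It names no study for this comparison.

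The Objectives section asks whether "healthy skin controls and PSO-patients differ regarding social anxiety and/ or the release of SP, IL-6 and IL-17 (study 2", the parenthesis going on to point to the SPIRIT schedule. Here the comparison belongs to study 2, and itch intensity is not among the outcomes.

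The Methods state that SIAS and SPS are completed in both studies, and that average and maximum itch over 24 hours are rated in both studies by patients and controls. Study 1 plans 250 patients and 250 controls. Study 2 plans 64 and 64, taken from study 1 participants who are interested in laboratory sessions of about 5.5 hours. Transmissible disease and treatment with biologicals are additional exclusions.

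The Statistical analyses section describes Spearman screening of control variables and a hierarchical regression of itch for study 1, in which "Social anxiety measured by the SIAS and SPS will be considered as predictor variable in step 2 of the analyses". For study 2 it says "To answer the research question of study 2, mediation analyses will be conducted using the SPSS macro PROCESS", with an exploratory regression on induced itch. It then adds: "Separate analyses will be conducted for patients and controls". The one group contrast in the Methods is high against low social anxiety by median split of SIAS, to see "whether these groups differ in itch intensity and the secretion of assessed neuroendocrine and inflammatory parameters".

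**The concern.** There are two linked problems.

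First, a comparison that can be made in the full study 1 sample is assigned to a subset about a quarter of its size. That subset has passed a further step of self-selection and stricter exclusions. The biologicals exclusion presumably removes patients far more often than controls, so the patients in study 2 represent psoriasis patients less well than those in study 1.

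Second, none of the models described contains a patient/control term, and each is fitted within one group. They estimate how social anxiety relates to itch inside a group, not how far the groups differ in social anxiety, itch or mediators.

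At stake is precision on a stated aim. A modest difference in social anxiety that study 1 would probably show could be missed in study 2 and reported as no difference. The two lists of aims also leave open whether itch is compared at all.

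**Working it through.** **1. Stated aim against described analysis**

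| Item | Abstract | Objectives | Models described |
|---|---|---|---|
| Social anxiety, patients vs controls | yes, no study named | yes, study 2 | no group term |
| Itch, patients vs controls | yes, no study named | not listed | no group term |
| SP, IL-6, IL-17, patients vs controls | yes, no study named | yes, study 2 | no group term |

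**2. The plan's own sample size**

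Inputs from Statistical analyses: f² = 0.10, α = 0.05, and β printed as 20, read here as 0.20.

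For one regression coefficient the non-centrality is √(f²·N). With N = 64 this is √6.4 = 2.53.
- One-sided test: power 0.804, and 64 is the smallest N that reaches 80%. This matches the stated size per group.
- Two-sided test: N = 81 is needed; power at 64 is 0.70.
- Omnibus F test with 4 predictors: N = 125, near the total of 128, but this would describe a pooled sample.

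The exact match is a within-group regression test. The article does not state sidedness, so this is an inference. The article gives no calculation for a patient-control difference.

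**3. Detectable patient-control difference**

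Two-sample t test, two-sided α = 0.05, 80% power, unadjusted. The normal approximation is d = (1.960 + 0.842)·√(1/n₁ + 1/n₂); the last column uses the non-central t distribution.

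| Sample | √(1/n₁ + 1/n₂) | Approximate d | Exact d |
|---|---|---|---|
| Study 2, 64 vs 64 | 0.1768 | 0.495 | 0.499 |
| Study 1, 250 vs 250 | 0.0894 | 0.251 | 0.251 |
| Study 1 as reported so far, 234 vs 174 | 0.1001 | 0.280 | 0.281 |

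**4. Power over a range of true differences**

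The article gives no expected difference, so these values of d are assumptions.

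| True d | 64 vs 64 | 250 vs 250 |
|---|---|---|
| 0.2 | 20% | 61% |
| 0.3 | 39% | 92% |
| 0.4 | 61% | 99% |
| 0.5 | 80% | >99% |

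**5. Itch model in controls (side point)**

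Other itchy conditions are excluded, so many controls may score zero on the itch scale. The share is not given and is assumed here. The correlations r come from a simulation of a left-censored normal outcome with latent r = 0.30. Power at n = 64 is approximately Φ(√61·atanh(r) − 1.96).

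| Share of zeros | Observed r | √61·atanh(r) | Power |
|---|---|---|---|
| none | 0.30 | 2.42 | 68% |
| 50% | 0.26 | 2.08 | 55% |
| 80% | 0.197 | 1.56 | about 35% |
| 95% | 0.129 | 1.01 | 17% |

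**The case against.** **The article is condensed.** The statistical section addresses each study's main research question, and the group comparison is introduced as an addition. The sentence on separate analyses follows the regression and mediation text and most naturally governs those models. The high/low social anxiety contrast has no named test either, so the section is visibly not a full list. A two-group test of a secondary aim may well stand in the full protocol or analysis plan. This stands. A reader might infer that the plan forbids a group comparison, or that the aim will get no valid test; the article supports neither.

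**The study 2 label may be a slip.** It rests on one parenthesis, and the Abstract names no study. This stands too, but it argues for reconciling the two texts.

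**Volunteer bias is not shown.** Participants in study 1 are volunteers as well, and both groups pass the same step into study 2. A biased difference would require selection that acts differently in patients and controls. It is possible, but nothing in the article demonstrates it.

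**No comparison of paths is proposed.** A reader might expect the authors to infer a group difference from a significant path in patients beside a non-significant one in controls. The stated aims compare levels, and no section proposes that inference.

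**The control mediation is not shown to fail.** Excluding itchy conditions does not exclude itch: controls rate 24-hour itch and answer an item on chronic itch. The share of zeros is unknown, and mediation is an aim in patients only. What remains is a caution about power.

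**Conclusion.** The point holds as a matter of placement and consistency. The Objectives assign the patient-control comparison of social anxiety to the smaller, more selected sample although study 1 collects the same scales. The two lists of aims disagree on itch, and the models described do not estimate a patient-control difference. Moving the comparison to study 1 halves the detectable difference, from d = 0.50 to d = 0.25; at the recruitment reported in the article it would be 0.28.

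These figures assume an unadjusted two-sided t test at 5% with 80% power and roughly normal outcomes. They do not carry over unchanged to an adjusted model or to an interaction. The reduced power of the itch mediation in controls depends wholly on the assumed share of zero scores and is a secondary remark. The change is worth making because it costs almost nothing; the main analyses in patients are unaffected.

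**What to change.** - Reconcile the Abstract and the Objectives: state which outcomes are compared between patients and controls, whether itch is one of them, and in which study.
- Compare social anxiety (SIAS, SPS) and itch between patients and controls in study 1. State that 250 vs 250 gives about 80% power for d = 0.25, two-sided.
- Compare SP, IL-6 and IL-17 in study 2 with group as the main term. Adjust for the person-related control variables already listed that apply to both groups: age, gender, BMI, smoking, oral contraceptives and social status. SA-PASI exists only in patients and cannot enter.
- Do not adjust this primary contrast for SIAS. The Introduction presents social anxiety as a possible consequence of psoriasis, so adjustment could remove part of the difference sought.
- State that an unadjusted 64 vs 64 comparison detects d = 0.50 with 80% power.
- If the relation of SIAS to a mediator is to be compared between groups, use a group by centred-SIAS term and label it exploratory.
- Note that the mediation in controls may be underpowered if many report no itch, and report the observed share of zeros.

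The cost is wording and a few additional models on data already being collected. No interim analysis is planned, so the change can be recorded before any results are seen.

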
### Ethics

The study was approved by the Institutional Review Board at the Department of Medicine at the Justus-Liebig-University of Giessen and by the State Medical Association of Hessia. Participants take part in this study voluntarily. They are informed about the study design and possible risks of the application of the suction blister method in detail and give their written consent before participation.

### Patient, public involvement and dissemination

Patients were not involved in planning of the study. However, members of the university, involving staff from multiple medical disciplines discussed the research project, and made suggestions how to improve the study design before a decision was made regarding funding of the study. These suggestions led to the inclusion of a healthy skin control group. Trial results will be disseminated by publication in scientific journals and by conference contributions.

## Discussion

To the best of our knowledge, the current research project is the first to investigate the role of *social* anxiety in PSO-patients in a very detailed manner. It will investigate if neuroendocrine and inflammatory parameters mediate the relationship between social anxiety and itch in these patients. This will shed light on the question if mental health issues contribute to disease burden in PSO-patients and whether this involves biomolecular processes that can worsen inflammation. State of the art validated methods and instruments will be used to answer these questions by combining self-report and minimally invasive biological sampling [65, 67, 72–74, 80–82]. The advantage of the employed biological sampling method, the suction blister method, is that it allows the determination of the inflammation and neuropeptidergic parameters IL-6, IL-17, and SP extracted directly from the skin. Most previous studies on neuro-immune interaction in skin were conducted in mice due to the sampling possibilities in this setting. Hence, the relationship between psychological factors, neuro-immune activation and symptoms of psoriasis can be studied in a human population in the here proposed setting.

Limiting factors of the current research project are that the biosampling procedure itself might possibly cause arousal. To rule out this possibility, participants will be informed about the suction blister method thoroughly in order to habituate to the application of this method. Therefore, we expect that neuroendocrine and inflammatory parameters can be determined in relation to their overall social anxiety condition. Due to the cross-sectional study design, conclusions regarding social anxiety as *cause* of itch cannot be drawn from the data [91]. Also, itch will be measured by self-report only and not by video-recording of scratching behavior. In general, participants must fulfill several inclusion criteria, which limits the external validity [92]. A typical PSO-patient might come with a variety of comorbidities that could conflict with a study design allowing a high internal validity. Overall, we are aiming for a moderate internal and external validity. Thus, we exclude participants who take certain medications (e.g. SSRIs, see Methods), but include individuals with highly prevalent conditions in PSO-patients, such as the metabolic syndrome [93]. In the current research project, we investigate whether social anxiety is a significant predictor of itch mediated by neuroendocrine and inflammatory parameters. Of no less importance may be the question whether itch leads to increased social anxiety. Thus, future prospective studies could e.g. investigate whether the relief of itch diminishes social anxiety mediated by visible lesions of the skin, such as marks or scars. The importance of consequences of scratching has already been shown in such a way that bleeding was the most relevant aspect linked to stigmatization in PSO-patients [94].
